#### 2.7.3. Lower Extremity Function

The modified Harris Hip Score (mHHS-Gr) and Lower Extremity Functional Scale (LEFS-Gr) will be used to determine lower extremity function. The mHHS [48] and LEFS [49,50] are valid and accurate self-reported measures of hip pain, function and lower extremity function. The mHHS has been used in femoral neck fractures with high discriminative capability between groups with and without complications at four months follow-up (95% CI Area Under the Curve: 0.63–0.89) and with good responsiveness from 4 to 12 months follow-up [51]. On the mHHS, one question assesses pain (score from 0–44) and seven questions functioning (score from 0–47). The total score will be multiplied by 1.1, resulting in a range from 0 to 100, with a score of 100 representing the worst possible hip pain and function. The LEFS comprises 20 multiple-choice questions scored on a 5-point scale (0–4: 0 = very high degree of difficulty to 4 = no difficulty, with a maximum score of 80). Assessment of the mHHS and LEFS will be performed on day 1 of admission to assess the pre-fracture level of independence (retrospective narrative) and at 4, 8, 26 and 52 weeks postoperatively.

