#### 2.7.5. Nutritional Status

To assess the patient’s nutritional status, the levels of albumin and prealbumin in the blood will be assessed. A blood sample will be collected and analyzed in the laboratory on the day of admission; one day before surgery; on the third postoperative day and at 1, 4, 8, 26 and 52 weeks postoperatively.

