vWF:Antigen (Ag) and vWF:Activity (Ac) are used as measures of platelet and endothelial dysfunction impacting the hemostatic equilibrium. The plasma levels of vWF:Ag and vWF:Ac will be measured using an automated latex enhanced immunoassay (HaemosIL^TM^ assay, Instrumentation Laboratory Corporation, Lexington, KY, USA) using IL (Instrumentation Laboratory) coagulation equipment (ACL TOP). The vWF:Ac will be evaluated by measuring the differences in turbidity caused by the latex reagent’s agglutination. A monoclonal anti-VWF antibody immobilized on the latex reagent interacts with the vWF in the blood sample. The agglutination is proportional to the vWF:Ac and is determined by the decreased light transmission resulting from the aggregates. The results will be presented as a percentage of the normality.

For the ROTEM analysis, within 90 min after blood collection, a citrated tube will be immediately filled with blood and will be analyzed in a ROTEM analyzer. Blood held at room temperature for up to 120 min after collection does not impact the ROTEM findings. Blood samples will be examined using a ROTEM analyzer (ROTEM delta, Tem Innovations GmbH). The ROTEM analysis includes preoperative EXTEM and INTEM testing and postoperative INTEM assays. The following EXTEM and INTEM parameters will recorded: clotting time (CT, seconds), the time from the beginning of measurement until the formation of a clot 2 mm in amplitude; clot formation time (CFT, seconds), the time from CT (amplitude of 2 mm) until a clot firmness of 20 mm was achieved; amplitude recorded at 10 min (A10, mm); an angle (a°), the angle between the central line and the tangent of the TEM tracing at the amplitude point of 2 mm describing the kinetics of clot formation; maximum clot firmness (MCF, mm), the final strength of the clot; and the lysis index at 60 min (LI60, %), which is the percentage of remaining clot stability in relation to the MCF following the 60-min observation period after CT, which indicates the speed of fibrinolysis [10].

Blood samples will be collected on the day of admission; one day before surgery; on the third postoperative day and at 1, 4, 8, 26 and 52 weeks postoperatively.

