#### 2.8.2. Data Analysis

Descriptive statistics will be used to summarize the baseline characteristics of the patients participating in each group. Continuous variables will be presented with the mean and standard deviation or median and interquartile ranges (IQR) if they do not follow a normal distribution. Categorical variables will be presented with absolute and relative frequencies (n, %). The Kolmogorov–Smirnov test will be performed to check for normality. Based on the normal or non-normal distribution of the sample, a *t*-test or Mann–Whitney test will be performed to compare the means or medians of the two groups, respectively. The chi-square test will be used to identify differences in the categorical variables between the two groups. A subgroup analysis will be performed a posteriori for the different surgical techniques used for all variables.

To detect confounding factors that may affect the functional tests (CAS, 6WMT and TUG), multiple linear regression will be performed after first performing the relevant check on whether the conditions are met to consider the linear regression results reliable. If the necessary conditions are not met, the necessary transformations of the dependent variables will be carried out.

To test the change of the parameters to be measured at multiple time points (e.g., albumin, functional score, etc.) and to compare the change between the intervention group and the control group, we will perform an analysis of variance for repeated measurements (repeated measures ANOVA).

Additionally, the time to occurrence of an event (e.g., death, readmission to hospital, thrombosis, etc.) will be presented with a Kaplan–Meier survival curve. To highlight the factors related to the time of occurrence of an event, semiparametric (Cox proportional hazard models) or parametric survival analysis models (e.g., Weibull, exponential, etc.) will be performed, as will result from the analysis that will be done.

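### Secondary outcomes with an admission value are compared by repeated measures ANOVA of change with no baseline covariate: valid, but less efficient than adjusting for that value

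*Protocol article*

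**What the plan says.** Section 2.8.2 (Data Analysis) names one method for outcomes followed over time. Its purpose is given as "To test the change of the parameters to be measured at multiple time points (e.g., albumin, functional score, etc". Repeated measures ANOVA is the method chosen, both for that test and for setting the two arms against each other. A t-test or Mann–Whitney test is also planned for two-group comparisons. The only model with covariates is for other outcomes: "To detect confounding factors that may affect the functional tests (CAS, 6WMT and TUG), multiple linear regression will be performed". None of those three has an admission value in Table 1.

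The outcomes that do have one are:

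- LEFS and mHHS (section 2.7.3): admission, then weeks 4, 8, 26 and 52, which is 5 time levels. The admission assessment "will be performed on day 1 of admission to assess the pre-fracture level of independence (retrospective narrative"), so it records recalled function before the fracture.
- Albumin and prealbumin (2.7.5): "A blood sample will be collected and analyzed in the laboratory on the day of admission; one day before surgery", then day 3 and weeks 1, 4, 8, 26 and 52, which is 8 levels (7 in Table 1, which has no tick for the day before surgery).
- Haemostatic factors (2.7.6): the same schedule as albumin.
- Lactate (2.7.4): admission, three intraoperative samples and 12 hours after surgery, which is 5 levels.

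**The concern.** Both examples in the ANOVA sentence, albumin and functional score, have an admission value, and a change needs a starting point. If admission is a level of the time factor, two things follow. The group main effect averages in a pre-treatment value that treatment cannot have altered, so it is diluted. The group-by-time test spreads the signal over 4 degrees of freedom (LEFS, mHHS, lactate) or up to 7 (blood markers). If admission is instead left out of the ANOVA, the baseline is not used at all. On either reading it is not used as a covariate to remove between-patient variance.

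For LEFS and mHHS there is a further point. Change from recalled pre-fracture function measures the shortfall from the earlier state, not the response to treatment. The recalled score is still a sensible covariate.

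These outcomes carry the secondary objectives on lower extremity function, nutrition, haemostasis and surgical stress. The trial was sized only for CAS and 6MWT, so they have no planned power to spare.

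**Working it through.** **The plan's own figure.** Section 2.8.1 uses a 50 m difference, SD 75, α = 0.05 (taken as two-sided) and 90% power. Per arm: 2 × (75/50)² × (1.960 + 1.282)² = 47.3, so 48 per arm and 96 in total, as stated. Then 96 × 1.2 = 115.2, giving 116. The 48 per arm is used below.

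**Assumptions.** The protocol gives no correlation, effect size or power for the affected outcomes. I take unit SD, the same correlation ρ between any two visits, no arm difference at admission, and a 0.5 SD effect.

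**One visit.** The noncentrality is 0.5 / √(2V/48), where V is 1 for a t-test on the later value, 2(1 − ρ) for a change score, and 1 − ρ² for the later value adjusted for admission.

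| ρ | V change | V adjusted | Later-value t-test | Change score | Adjusted |
|---|---|---|---|---|---|
| 0.3 | 1.40 | 0.91 | 68% | 54% | 72% |
| 0.5 | 1.00 | 0.75 | 68% | 68% | 80% |
| 0.7 | 0.60 | 0.51 | 68% | 88% | 92% |

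The efficiency of the change score relative to adjustment is (1 − ρ²) / [2(1 − ρ)] = (1 + ρ)/2, that is 0.65, 0.75 and 0.85. Adjustment is better at every ρ below 1. Against the better of the two unadjusted tests the gain is about 4, 12 and 4 points.

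**Five time levels, effect constant at all four later visits.**

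- Group-by-time: the arm differences 0, 0.5, 0.5, 0.5, 0.5 have mean 0.4 and sum of squares 0.16 + 4 × 0.01 = 0.20. The noncentrality is 24 × 0.20 / (1 − ρ), on 4 df.
- Group main effect: effect 0.4, variance (1 + 4ρ)/5.
- Later-visit mean adjusted for admission: effect 0.5, variance (1 + 3ρ)/4 − ρ².

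| ρ | Group-by-time | Main effect | Adjusted mean |
|---|---|---|---|
| 0.3 | 52% | 83% | 97% |
| 0.5 | 69% | 71% | 98% |
| 0.7 | 91% | 60% | >99% |

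The group-by-time test trails the adjusted mean by about 45, 29 and 9 points.

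**Splitting that gap at ρ = 0.5.** A one-df contrast of the later mean minus admission has variance 1.25(1 − ρ) = 0.625 and 87% power. So 69% to 87% (18 points) comes from degrees of freedom, and 87% to 98% (11 points) from how the baseline is handled. A joint 4-df test with baseline adjustment gives 91%.

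**An effect that wanes.** Take 0.5, 0.5, 0.25 and 0 SD at weeks 4, 8, 26 and 52, with ρ = 0.5. The five differences have mean 0.25 and sum of squares 0.25, so the noncentrality is 24 × 0.25 / 0.5 = 12 and group-by-time power is 80%. The adjusted average (effect 0.3125, variance 0.375) has 70%. The adjusted difference at week 8 alone has 80%, and the joint baseline-adjusted test 87%. At ρ = 0.7, group-by-time has 96%, the adjusted average 81% and the adjusted week-8 difference 92%.

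**The case against.** The strongest reply has four parts.

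1. The article never says that admission is a level of the time factor, and it does not exclude covariates. A condensed article may leave model terms to a fuller plan. It stands that the reading is inferred. But the article does commit to a method and names covariates only for other outcomes, so improving that method is a fair suggestion.
2. Repeated measures ANOVA is valid in a randomised trial. This stands: the issue is efficiency, not bias or contradiction.
3. The large gaps set an omnibus test against a one-df average under a constant effect, the pattern that suits averaging best. This stands. The programme ends at 8 weeks and follow-up runs to 52, so waning is plausible, and the planned group-by-time test can then equal or beat a baseline-adjusted average or single-visit comparison. Baseline adjustment still helps when like is compared with like (87% against 80% in the waning example).
4. The planned t-test already has 68% power at one visit, so at ρ = 0.3 the gain is 4 points, not the 18 seen against the change score. This stands too, and it is why the gain is quoted against the better unadjusted test.

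A reader might infer that the plan throws away much of its power, or that the trial's main conclusions are at risk. The documents do not support either. They give no correlation or effect size for these outcomes. At a correlation of 0.8, or at the 0.67 SD used for 6MWT with a correlation of 0.7 or more, the group-by-time loss under a constant effect is about 1.5 points or less. Neither primary outcome has an admission value.

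**Conclusion.** The point holds as an efficiency improvement for secondary outcomes. Section 2.8.2 specifies an analysis of change for outcomes with an admission value and names no adjustment for it. With 48 per arm and a 0.5 SD effect at one visit, adjustment is worth about 4 to 12 power points over the better of a later-value t-test and a change score, for correlations of 0.3 to 0.7. The larger shortfall of the group-by-time test, about 9 to 45 points, arises only if the effect is the same at every visit and is tested as an average, and much of it is degrees of freedom. The group main effect is diluted by the pre-treatment level whatever the pattern. All these sizes rest on assumed correlations, effect and equal variances. The comparisons of 3-day CAS and 8-week 6MWT, and the sample size of 116, do not change.

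**What to change.** In section 2.8.2, for each outcome with an admission value, take that value out of the response. Model the post-admission visits with arm, visit, arm-by-visit and the admission value of the same outcome as covariate. For LEFS and mHHS the covariate is the recalled pre-fracture score, and it should be described as such.

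Fix in advance, for each outcome, the visit of interest, and report the adjusted arm difference there. The average over post-admission visits should be a supplementary summary only, because it loses power if the effect wanes after week 8. If the sponsor wants an overall test, a joint test of the arm differences across visits comes from the same model.

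The cost is a change of wording. All values are already collected, and no patients, visits or samples are added.

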## 2. Materials and Methods

### 2.1. Study Design

The study protocol has been prospectively registered in the open database for study protocols, ClinialTrials.gov (registration number: NCT05389800) [33]. The study received approval number 402/26-7-2021 from the Institutional Review Board of the “Attikon” University Hospital (1st Department of Orthopaedic Surgery, National and Kapodistrian University of Athens) 7 September 2021.

A parallel group, single-blinded, randomized controlled trial (RCT) will be conducted with two groups of hip fracture patients. The sample will be recruited from a tertiary University Hospital (1st Department of Orthopaedic Surgery, “Attikon” University Hospital, Athens, Greece). The randomization will be done at the time of admission of the patients to the emergency department (ED) and after their written informed consent form. The study protocol’s instructions will be described through an informed consent form in plain language, along with all the procedures the subjects will undergo and the risks and benefits of participation. Allocation concealment will be ensured by using sequentially numbered, opaque, sealed envelopes. The envelopes were created by a biostatistician, who will participate actively in neither the delivery of any intervention nor in the outcome measures assessment. For the preoperative program, 116 patients need to be recruited, who will be randomized with a ratio of 1:1 using the block randomization method (58 in the intervention group and 58 in the control group). Immediately after the surgery, the participants of each group will continue in the postoperative intervention program: the intervention group (IG) will continue with the exercise program three times a week for a total of 8 weeks, while the control group (CG) will not receive any intervention at any time point after surgery (Figure 1, graphic illustration).

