## 3. Discussion

This study has two primary purposes. First, to study the effect of a preoperative aerobic exercise program with a portable upper extremity cycle ergometer on immediate postoperative mobility. Second, to investigate the additional effect of an 8-week postoperative aerobic exercise program with a portable upper extremity cycle ergometer on the walking distance at 8 weeks after surgery. This study also has a number of secondary objectives. Regarding the preoperative exercise program evaluation of the effect of the preoperative program on surgical stress (via blood lactate levels), perioperative bleeding and transfusion requirements, hemostasis factors will be evaluated, in addition to, an evaluation of the effect of the postoperative program in the short and long term: lower extremity functionality, aerobic capacity, nutritional status, hemostasis factors, mortality, rehospitalization and complications related to surgery and hospitalization (thrombotic and thromboembolic events).

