## Figures and Tables

**Figure 1 biomedicines-11-01263-f001:**
[figure not shown]
Graphical illustration of the study design. In the frame “outcomes”, only the first integration of the assessments and not the follow-up assessment can be seen. For example, mHHS will be assessed not only at admission (first integration as shown in the box) but also at 4, 8, 26 and 52 weeks (follow-up assessment). Accordingly, the evaluation of the basic mobility through the CAS scale will be evaluated on the first; second and third postoperative day and at 4, 8, 26 and 52 weeks postoperatively. Blood samples will be collected on the day of admission; one day before surgery; on the third postoperative day and at 1, 4, 8, 26 and 52 weeks postoperatively. Analysis of the coagulation biomarkers will be done by ROTEM. After the 8 weeks of postoperative intervention, there will be no intervention for any of the two groups. The time from admission to surgery will vary. Created with BioRender.com (accessed on 16 April 2023). Abbreviations: MIIT = Moderate Intensity Interval Training; CAS = Cumulative Ambulation Score; 6MWT = six-minute walk test; TUG = Timed-Up and Go; mHHS = modified Harris Hip Score; LEFS = Lower Extremity Functional Scale; NMS = New Mobility Score; La = Lactate concentration of capillary blood; ROTEM = rotational thromboelastometry; Hemostatic profile = tissue Plasminogen Activator (tPA); Plasminogen Activator Inhibitor-1 (PAI-1); Endogenous Thrombin Potential (ETP); Fibrinogen; D-dimers; von Willebrand factor antigen; von Willebrand factor activity; Thrombin–Antithrombin Complex (TAT); Thrombomodulin; platelet function—PFA-100; hemostatic profile using viscoelastic techniques—ROTEM; pre-op = preoperative; peri-op = perioperative; post-op = postoperative.

**Table 1 biomedicines-11-01263-t001:** Time points of the outcome measurements. In bold are the primary outcome measures for which the sample size was calculated for the effects of the preoperative and the postoperative exercise program.

Outcome Measures	1st Day of Admission	One Day before Surgery	During Surgery	Post-Op—to Discharge	4th Week Post-Op	8th Week Post-Op	26th Week Post-Op	52nd Week Post-Op
**CAS**				**1st, 2nd, 3rd post-op**	**✓**			
**6MWT**					**✓**	**✓**	**✓**	**✓**
TUG					✓	✓	✓	✓
mHHS	✓				✓	✓	✓	✓
LEFS	✓				✓	✓	✓	✓
NMS	✓							
La	✓		✓	12 h post-op				
Nutrional status	✓			3rd post-op	1st and 4th wk	✓	✓	✓
Hemostatic factors	✓			3rd post-op	1st and 4th wk	✓	✓	✓

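### An ANOVA of change over eight haemostasis samples cannot say which exercise programme acted, although each programme has its own haemostasis objective

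*Protocol article*

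**What the plan says.** Section 3 (Discussion) lists the secondary objectives by programme. Under the preoperative programme it says "perioperative bleeding and transfusion requirements, hemostasis factors will be evaluated". It then adds "an evaluation of the effect of the postoperative program in the short and long term: lower extremity functionality, aerobic capacity, nutritional status, hemostasis factors", among other outcomes. Haemostasis thus appears under both programmes. The Expected Outcome section gives the preoperative programme its own haemostatic hypothesis and links it to faster recovery of mobility right after surgery.

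Section 2.7.6 sets the sampling: "Blood samples will be collected on the day of admission; one day before surgery; on the third postoperative day and at 1, 4, 8, 26". The list closes with a sample at week 52. That is two samples before surgery and six after it. The Figure 1 caption agrees. The row "Hemostatic factors" in Table 1 has no tick in the day-before-surgery column.

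Section 2.8.2 assigns repeated-measures ANOVA to parameters measured at several time points, "to compare the change between the intervention group and the control group". Its examples are albumin and functional score; haemostasis is not named but fits the description. The period of change is not given. The same section mentions a t-test or Mann–Whitney comparison of the two groups, also without a time point or programme.

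Section 2.1 describes a single randomisation at admission. After surgery the intervention arm continues to exercise for eight weeks and the control arm receives no study intervention.

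**The concern.** The protocol states two questions about haemostasis and names a method that does not separate them. An arm-by-time test responds to a difference in profile at any of the eight samples. Only the sample on the day before surgery follows the preoperative programme alone. The six later samples follow both programmes, and weeks 26 and 52 come after all study exercise has ended.

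At stake is the conclusion that preoperative exercise changes clotting before surgery. If a significant arm-by-time result were read as support for it, that claim could rest entirely on differences that arose after surgery.

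**Working it through.** **The plan's own figure.** The protocol gives no power figure for haemostasis. Its only sample size basis is for the primary outcomes, and the 6MWT calculation reproduces: n = 2 × (1.960 + 1.282)² × 75² / 50² = 47.3, so 48 per arm; 48 × 1.2 = 57.6, so 58 per arm and 116 in total. The point below does not depend on this figure except as the ceiling on the number analysed.

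**Inputs.**
- From section 2.7.6: T = 8 samples.
- From section 2.1: two arms, 58 each.
- Assumed, not in the documents: n = 52 analysed per arm (about 58 × 0.9 = 52.2), equal within-patient correlation ρ of 0.3 or 0.5, constant SD, effects d in SD units, two-sided 5% level.

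**Formula.** For the arm-by-time F test, the degrees of freedom are T − 1 = 7 and (2n − 2)(T − 1) = 102 × 7 = 714, with critical value 2.022. If the arms differ by d at k of the 8 samples, the noncentrality is

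λ = (n/2) × d² × k(1 − k/8) / (1 − ρ).

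**Purely postoperative effect.** Take an effect at day 3 and weeks 1, 4 and 8 (k = 4) and none before surgery. Then λ = 52 × d² / (1 − ρ). The smallest case is 52 × 0.09 / 0.7 = 6.69; the largest is 52 × 0.25 / 0.5 = 26.0.

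| ρ | d = 0.3 | d = 0.4 | d = 0.5 |
|---|---|---|---|
| 0.3 | 0.417 | 0.700 | 0.902 |
| 0.5 | 0.575 | 0.861 | 0.978 |

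The test is significant in 42% to 98% of trials although the preoperative programme did nothing.

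**Can a contrast tell the programmes apart?** A simulation used 4,000 runs, 58 per arm, ρ = 0.5 and d = 0.5 at two samples. The proportions of runs rejecting were:

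| True effect | Arm-by-time test | Change, admission to day before surgery | Change, admission to week 8 |
|---|---|---|---|
| None | 4.9% | 5.0% | 5.4% |
| Preoperative only (day before surgery, day 3) | 94.8% | 75.9% | 4.9% |
| Postoperative only (weeks 4 and 8) | 94.8% | 4.8% | 75.1% |
| Preoperative only, delayed to weeks 4 and 8 | 94.9% | 5.1% | 77.1% |

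The global test behaves the same whichever programme acted. The contrast within the preoperative period separates the first two active cases. The last two rows cannot be told apart by any of these tests, because the arm that exercised before surgery is the arm that exercised after it. The data at week 8 therefore speak only to the two programmes together.

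**The sample this depends on.** Section 2.7.6 and the Figure 1 caption include a day-before-surgery sample; Table 1 as read does not. If Table 1 governs, the admission sample is the only one before surgery, and no haemostasis comparison isolates the preoperative programme.

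**The case against.** The strongest reply is that this treats brevity as a rule. Section 2.8.2 does not say that one ANOVA will cover all eight samples, or that either programme will be judged by a global p-value. Repeated-measures ANOVA allows contrasts at chosen times, and an analysis plan that is not shown may name them. The t-test or Mann–Whitney sentence could be applied at the day-before-surgery sample. The primary outcomes are already tied to time points: the 3-day CAS and the 6MWT at week 8.

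Much of this stands. The ANOVA is not strictly the only comparison stated, and the protocol does not announce a wrong inference. What remains is that it names a method for repeated parameters, states two programme-specific objectives, and links neither the ANOVA nor the two-group test to either of them. That mismatch is visible in the article itself and is easily removed.

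A reader might also infer that the global test wastes power by spreading a preoperative effect over eight samples. The documents do not support this. It holds only if the effect disappears at surgery: with an effect at the day-before-surgery sample alone (d = 0.4 to 0.5, 52 per arm), the global test has 32% to 68% power against 56% to 83% for the single comparison adjusted for admission. If the effect lasts to day 3 (k = 2), the global test has 55%, 78%, 73% and 92%, against 56%, 75%, 65% and 83% for the single comparison (ρ = 0.3 then 0.5, with d = 0.4 then 0.5 within each). The gap closes or reverses. The Expected Outcome section, which expects the preoperative effect to help recovery just after surgery, fits persistence better than disappearance.

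**Conclusion.** The point holds as one of attribution. With one randomisation and both programmes in the same arm, an arm-by-time result over the eight haemostasis samples cannot be credited to the preoperative programme. Under the assumptions above, a purely postoperative effect of 0.3 to 0.5 SD would make it significant in 42% to 98% of trials. The range moves with the assumed correlation, number analysed and effect pattern; the failure of attribution does not.

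It is not a finding about lost power. Nor is it wholly a matter of analysis: a reader might infer that a better contrast would also isolate the postoperative programme, but without a second randomisation none can. It concerns secondary outcomes only and is a worthwhile improvement at no data cost.

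**What to change.** 1. Reconcile Table 1 with section 2.7.6 and the Figure 1 caption on whether haemostasis is sampled on the day before surgery. The next step depends on that sample.
2. For the preoperative objective, name the arm difference at the day-before-surgery sample, adjusted for the admission value. For lactate, which section 2.7.4 schedules at admission and at the beginning of surgery, use the start-of-surgery sample in the same way.
3. Report the arm difference at week 8 as the effect of the combined pre- and postoperative programme, and say that the postoperative programme alone cannot be isolated in this design.
4. Report the other samples descriptively with confidence intervals, and base neither programme's claim on the global arm-by-time test.

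If the day-before-surgery sample is already being taken, the cost is a few sentences in section 2.8.2 and a corrected table. If it is not, step 2 cannot be run for haemostasis, and the preoperative haemostasis objective should be reworded to what the samples can show.
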